### Concealment mechanism {16b}

The randomization results of patients are put in sealed envelopes. At visit 5 (3-month follow-up), unblinded investigators will open the envelopes to go through interventions (intravitreal injections or micropulse laser or sham treatment).

### Implementation {16c}

The unblinded investigators will generate the allocation sequence and assign participants to interventions. The blinded investigators will enroll participants.

## Assignment of interventions: Blinding

### Who will be blinded {17a}

Investigators responsible for follow-up evaluation, technicians who operate OCT, and data analysts are blinded. When intervention is required, the patient will either receive intravitreal injections plus sham micropulse laser treatment, or micropulse laser plus sham intravitreal injections. Therefore trial participants are blinded throughout the study. Only the investigators qualified for laser treatment and intravitreal injections are unblinded.

### Procedure for unblinding if needed {17b}

In case of severe vision loss due to exacerbation of DME and requiring additional treatment or severe adverse reactions, subjects will be arranged to leave the study. The subjects who leave the group will be unblinded.

## Data collection and management

### Plans for assessment and collection of outcomes {18a}

Professional technicians will be responsible for FFA, OCT examination, and visual acuity examination. OCT was performed using Spectralis (Spectralis HRA+OCT; Heidelberg Engineering, Heidelberg, Germany). FFA was performed using HRA2 (Heidelberg Retinal Angiograph, Heidelberg Engineering, Heidelberg, Germany).

### Plans to promote participant retention and complete follow-up {18b}

Investigators will contact patients 2 (± 1) days before each visit to promote patients’ retention and complete follow-ups. And we will also arrange follow-up visits at the outpatient clinic to support patients with subsequent treatment if they decide to drop out of the study.

### Data management {19}

Data such as BCVA, IOP, and adverse events will be uploaded to the Electronic Data Capture (EDC) system.

### Confidentiality {27}

Patients will be numbered instead of their names. Personal information will be collected through these numbers. We will keep patient study records confidential as required by law. Relevant laws in our country provide guarantees for the security of privacy, data, and authorized access. The name, ID number, address, telephone number, or any information that can directly identify the patient in the study records will not be disclosed outside the Beijing Hospital unless required by relevant laws.

### Plans for collection, laboratory evaluation, and storage of biological specimens for genetic or molecular analysis in this trial/future use {33}

Not applicable. There are no biological specimens.

## Statistical methods

### Statistical methods for primary and secondary outcomes {20a}

The randomized set will consist of all randomized patients.

Full Analysis Set (FAS): Consists of all patients in the randomized set who are assigned to study treatment. They will be analyzed according to the treatment assigned to the subjects at randomization and the intention-to-treat principle.

Per Protocol Set (PPS): Consists of all patients in the full analysis set who complete the trial, had no significant protocol violations, and had no events that would confound the interpretation of the analysis. The analysis of the primary variable will be performed on the full analysis set.

For continuous and ordered categorical variables, analysis of variance (ANOVA) or analysis of covariance models which are both with baseline assessment as covariates were used to compare the changes between each treatment group and the baseline. Stratified and unstratified Cochran Mantel-Haenszel tests were also considered.

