**Methods:**

This study is a prospective randomized double-blind controlled clinical trial (RCT) in patients with DME. After 1-year follow-up, visual acuity and macular edema regression will be compared between micropulse laser combined with ranibizumab group and ranibizumab monotherapy group to determine whether the efficacy of micropulse laser combined with ranibizumab treatment was not lower than that of ranibizumab monotherapy in the treatment of DME. Visual acuity measured by the ETDRS chart is the primary outcome measure. The secondary outcome measures are CMT (central macular thickness) measured by OCT (optical coherence tomography) and the number of injections of two groups. Changes in visual acuity and CMT of the two groups will be compared at 12-month follow-up. Before patients are recruited, we provide them with informed consent, in which we explain to them the purpose and process of the study.

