### Objectives {7}

The purpose of this study is to evaluate the safety and efficacy of micropulse laser combined with intravitreal ranibizumab injections in the treatment of DME. Study subjects are 72 patients (more patients may be recruited) diagnosed with diabetic macular edema. By using a prospective randomized double-blind controlled study method, we hope to compare the changes of visual acuity and macular edema regression between micropulse laser combined with ranibizumab group with ranibizumab monotherapy group to determine whether the efficacy of micropulse laser combined treatment group in the treatment of DME is not lower than ranibizumab monotherapy and whether these two therapies are equally effective. Our goal is to reduce the number of intraocular injections and establish a new technique for the treatment of DME.

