### Trial design {8}

This study is a prospective, single-center, randomized controlled, double-blinded non-inferiority clinical trial. A flow chart of the study design is shown in Fig. 1. Study subjects are 72 patients (more patients may be recruited) diagnosed with diabetic macular edema.

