#### Primary outcome measure

BCVA: Best corrected visual acuity is measured using standard ETDRS protocol at baseline and every follow-up visit. Changes in visual acuity will be compared between the two groups at a 12-month follow-up.

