### Sample size {14}

Using two-sided test, with αas 0.05, changes of visual acuity as less than 5 letters between two groups, standard deviation as 6.53 (REVEAL study [12] as reference), enrolling 56 cases of subjects can set the power to 90%. Considering drop out, set the lost follow-up rate as 20%, then the final sample size is calculated as 72 subjects, with 36 subjects in micropulse laser combined with ranibizumab group and 36 subjects in the ranibizumab monotherapy group.

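### Non-inferiority is declared, but the stated analysis has no margin or confidence-interval rule, so it does not test the declared hypothesis

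*Protocol article*

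**What the plan says.** Trial design {8} describes a "randomized controlled, double-blinded non-inferiority clinical trial". The abstract's Methods paragraph aims to determine whether efficacy "was not lower than that of ranibizumab monotherapy in the treatment of DME". Objectives {7} asks whether the combined treatment "is not lower than ranibizumab monotherapy and whether these two therapies are equally effective", which adds an equivalence aim to the non-inferiority aim.

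Under Primary outcome measure, BCVA is handled thus: "Changes in visual acuity will be compared between the two groups at a 12-month follow-up".

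Statistical methods {20a} gives ANOVA or ANCOVA with the baseline assessment as covariate. These models "were used to compare the changes between each treatment group and the baseline"; Cochran-Mantel-Haenszel tests are mentioned as a further possibility. The section defines a full analysis set and a per-protocol set, then says: "The analysis of the primary variable will be performed on the full analysis set".

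The only figure resembling a margin is in Sample size {14}. That section assumes a two-sided test at 0.05, "changes of visual acuity as less than 5 letters between two groups", an SD of 6.53 and 90% power with 56 subjects, raised to 72 for 20% loss to follow-up.

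**The concern.** A non-inferiority conclusion needs three things: a between-group contrast, a margin, and a rule that sets the confidence limit against the margin. The design and objectives promise the conclusion, but the analysis section supplies a model and no rule. The 5 letters stay in the sample-size section, attached to a two-sided test.

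Neither outcome of a plain difference test answers the question. A significant difference in favour of the combination would show superiority. A non-significant one shows only that the data did not separate the arms, which becomes more likely as the SD rises or patients are lost. The trial's main conclusion is at stake, because someone reading the result could take non-significance as proof that the combination is not lower, and nothing in the article rules this out.

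**Working it through.** **Inputs.** From Sample size {14}: 5 letters, SD 6.53, two-sided alpha 0.05, 56 evaluable (28 per arm), 72 enrolled (36 per arm). From Trial design {8}: non-inferiority. Assumption: the 5 letters are the margin, which the article does not say. The difference is Group I minus Group II, so negative values mean the combination is worse.

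**Step 1: the plan's own figure.** Per-arm n = 2 × [6.53 × (1.960 + 1.282) / 5]² = 35.8, so 36 per arm or 72 evaluable for 90% power. The same n follows for non-inferiority at one-sided 0.025 with true difference 0. The stated 56 is not reproduced: at 28 per arm the power is 81.7% by the normal approximation and 80.3% by the noncentral t.

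**Step 2: precision.** SE = 6.53 × √(2/n).
- 28 per arm: SE = 1.745; t(0.975, 54) = 2.005; 95% CI half-width = 3.50 letters. To exclude −5, the observed difference must be better than −5 + 3.50 = −1.50.
- 36 per arm: SE = 1.539; t(0.975, 70) = 1.994; half-width = 3.07. The threshold is −5 + 3.07 = −1.93.

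**Step 3: false passes at a true difference of −5.** If non-significance is taken as not lower, the pass probability is P(|T| < t(0.975, df)), where T is noncentral t with parameter −5/SE (−2.865 at 28 per arm, −3.249 at 36).

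| Rule | 28 per arm | 36 per arm |
|---|---|---|
| Non-significant difference test | 19.7% | 10.7% |
| Lower 95% limit above −5 | 2.5% | 2.5% |

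The normal approximation gives 18.3% and 9.9% for the first row.

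**Step 4: sensitivity to SD.** At assumed SDs of 8, 10 and 12 with 28 per arm, the first row becomes 37%, 55% and 67%. The second stays at 2.5%. The difference-test reading becomes more lenient as the data get noisier.

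**Step 5: what the proper rule costs.** At true difference 0, SD 6.53 and a 5-letter margin, the CI rule has 80.3% power with 56 evaluable and 89.3% with 72 (81.7% and 90.1% by the normal approximation). Requiring the whole 95% CI to lie within ±5, as an equivalence claim would, has power of about 63% with 56 and 80% with 72 (normal approximation).

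**The case against.** The strongest reply is that the ingredients are already there. A baseline-adjusted ANCOVA yields an adjusted between-group difference with a CI, the two-sided 0.05 implies a 95% interval, and 5 letters could serve as the margin. An analysis plan that is not shown may join them. This stands as far as the model goes: no different model is needed. It does not remove the mismatch. The margin and the decision rule define the hypothesis of a non-inferiority trial, and the article states an analysis that does not test it.

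Four stronger readings are tempting, and the article does not support them:

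- **That the primary comparison is within groups.** The wording of {20a} invites this, but the primary-outcome section says the groups are compared with each other, and baseline as a covariate fits a between-group model of change. The phrase needs correcting; it does not show that no between-group comparison is planned.
- **That non-significance is the only route to a positive conclusion.** No section says non-significance will be read that way, and the ANCOVA can supply a between-group CI. The 20% and 11% are therefore conditional.
- **That passes at a true 4-letter deficit are also errors.** Four letters lies inside a 5-letter margin, so those passes would be correct.
- **That the per-protocol set will go unused.** It is defined and given no stated role for the primary variable, but supporting analyses are commonly left to the analysis plan. This is a secondary point.

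**Conclusion.** The concern holds as a mismatch between the declared hypothesis and the stated analysis. The article promises non-inferiority, and in one place equal effectiveness, but gives no named margin and no rule setting a confidence limit against it.

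The size is conditional. If non-significance were taken as not lower, about 20% of trials with 28 per arm (11% with 36) would pass a combination that is truly 5 letters worse, instead of 2.5%. This assumes that 5 letters is the margin and that the SD is 6.53; a larger SD makes it worse. The mismatch itself needs none of these assumptions.

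**What to change.** In Statistical methods {20a}, replace the sentence on comparing groups with baseline by wording such as: *The primary analysis is an ANCOVA of month-12 BCVA change with treatment and baseline BCVA. The adjusted difference (Group I minus Group II) is reported with a two-sided 95% CI. Non-inferiority is concluded only if the lower limit lies above minus M letters.* The sponsor must name M and justify it, and should say whether the 5 letters of Sample size {14} were meant as M.

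Also:
- Report the same CI in the already defined per-protocol set as a supporting analysis.
- In Objectives {7}, delete the equal-effectiveness aim, or allow it only if the whole CI lies within ±M.
- Fix the rule before unblinding for analysis and disclose the date. Trial status gives recruitment from January 2019, so a margin named now is late and readers should be told.

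The change needs no new model and no new measurements, but it has a cost in power. At a 5-letter margin, SD 6.53 and true difference 0, the rule has about 80% power with 56 evaluable patients and about 89–90% with 72. The 90% stated for 56 should be restated. Holding 90% under the plan's 20% loss would mean 72 / 0.8 = 90 enrolled.

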### Interim analyses {21b}

The research committee of capital clinical characteristic application research and Beijing Hospital will meet over one year after the study started enrolling as the interim evalution. If assessment objectives are met, the study may continue.

### Methods for additional analyses (e.g., subgroup analyses) {20b}

Stratification will be made according to DME type and baseline BCVA classification: focal vs. diffuse, baseline BCVA ≤ 60 letters vs. > 60 letters.

### Methods in analysis to handle protocol non-adherence and any statistical methods to handle missing data {20c}

For missing values, the analysis will follow the LOCF (last observation carried forward) approach to obtain approximate results. If the patient dropped out, data of the last post-baseline observation during follow-up will take place of the missing data. If there were intermediate missing values (i.e., one missed visit during follow-up, then the patient resumed the visit), these values will be replaced with the mean value of the previous observation and the first subsequent observation.

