#### Screening period: from day −14 to day −1

At screening (visit 1, between day −14 and day −1), after signing the informed consent (the model consent form is attached as a supplementary file), the patient is enrolled in the study and will undergo a series of examinations including ETDRS (Early Treatment Diabetic Retinopathy Study) visual acuity test, intraocular pressure measurement, slit-lamp, and indirect ophthalmoscopy, optical coherence tomography (OCT), optical coherence tomography angiography (OCTA), fundus fluorescein angiography (FFA), fundus color photography, vital signs, hematology, urinalysis, blood biochemistry, and glycosylated hemoglobin to assess eligibility for the study.

#### Treatment period: from day 1 to month 11

At baseline (visit 2, day 1), eligible patients will be randomized by 1:1 ratio into micropulse laser combined with ranibizumab group or ranibizumab monotherapy group. After baseline visit, all patients receive 3 consecutive monthly ranibizumab injections. Subjects will then return to the study site on day 90 (± 7 days) and according to the retreatment criteria, patients will either receive micropulse laser and sham intravitreal ranibizumab or sham micropulse laser and intravitreal ranibizumab. Thereafter, subjects will return to the study site every 30 days (± 7 days) for assessment (schedule shown in Fig. 2) and accept appropriate treatment according to the retreatment criteria.

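### LOCF for month-12 BCVA, in a non-inferiority trial whose arms are treated alike until day 90, is likely to be anti-conservative if drop-out is roughly balanced

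*Protocol article*

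**What the plan says.** - Trial design {8} describes a "double-blinded non-inferiority clinical trial".
- Primary outcome measure, under Outcomes {12}: "Changes in visual acuity will be compared between the two groups at a 12-month follow-up". BCVA is recorded at baseline and at every follow-up visit.
- The missing-data section {20c} states that "the analysis will follow the LOCF (last observation carried forward) approach to obtain approximate results". For a patient who drops out, "data of the last post-baseline observation during follow-up will take place of the missing data". Any post-baseline visit qualifies, however early.
- The treatment-period text under Trial design {8} says that "all patients receive 3 consecutive monthly ranibizumab injections". Concealment mechanism {16b} shows when the arms can first differ: "At visit 5 (3-month follow-up), unblinded investigators will open the envelopes". After that, treatment differs only for patients who meet the retreatment criterion.
- Sample size {14} plans for loss: "Considering drop out, set the lost follow-up rate as 20" per cent. Trial status reports that losses have occurred and that further patients were recruited because of them, without giving numbers or timing.
- Statistical methods {20a} places the primary analysis on the full analysis set, so drop-outs enter it with their carried values.
- Section {11b} takes a patient out of the study after a fall of 15 letters or more since the last visit caused by worsening DME.

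**The concern.** LOCF puts an earlier visit in place of the month-12 outcome. In this design the early visits cannot separate the arms. Until day 90 everyone has had the same treatment, so the expected between-arm difference in a value carried from months 1 to 3 is exactly zero. A value from the next few months reflects only what has accrued since. If Group I is truly worse at month 12, those carried values dilute the deficit.

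In a superiority trial, dilution mostly costs power. In a non-inferiority trial it moves the estimate away from the margin and makes a false claim of non-inferiority easier. The common three-month loading phase is what makes this more than a general dislike of LOCF.

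**Working it through.** **Plan's own figure.** The article gives no figure for the effect of LOCF. The inputs come from Sample size {14}: 5 letters, SD 6.53, two-sided α 0.05 (2.5% in the non-inferiority direction), 36 per arm and 20% loss. The stated 90% power with 56 evaluable patients does not reproduce: 28 per arm gives about 82% by the normal approximation. That is a separate matter and does not enter the check below.

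**Assumptions.** The 5 letters are the non-inferiority margin (the article does not use that word). The test compares the lower 95% confidence limit with −5. Drop-out is balanced between arms and unrelated to outcome. The timing of drop-out and the speed at which the arms diverge are also assumed, because the article gives neither.

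**Formulas.** Let d be the share who drop out and f the average share of the month-12 difference already present at their last visit.

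- Expected estimate at a true difference of −5: E = −5 × [1 − d(1 − f)]
- Standard error: SE = 6.53 × √(2/36) = 1.54
- False non-inferiority rate: Φ((5 + E)/SE − 1.96)

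**Values of f.** With linear divergence from month 3 to month 12, the share present at month k is (k − 3)/9, and zero up to month 3. For last visits spread evenly over months 1 to 11, f = (1/9 + … + 8/9)/11 = 4/11. For months 4 to 11 only, f = 4/8 = 0.5. If the full difference appears at month 4, even spread gives f = 8/11.

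**Results, d = 20%.** The first row in full: E = −5 × 0.8 = −4.0, and Φ(1.0/1.54 − 1.96) = Φ(−1.31) = 9.5%.

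| Assumed drop-out and divergence | f | E | Rate, formula | Rate, simulated |
|---|---|---|---|---|
| All leave by month 3 | 0 | −4.00 | 9.5% | 8.9% |
| Even over months 1–11, linear divergence | 0.364 | −4.36 | 6.1% | 6.2% |
| All leave in months 4–11, linear divergence | 0.50 | −4.50 | 5.1% | 5.0% |
| Even over months 1–11, full difference from month 4 | 0.727 | −4.73 | 3.7% | 3.7–3.8% |
| No drop-out | – | −5.00 | 2.5% | 2.4% |

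**Sensitivity to d.** With everyone leaving by month 3, the rate is 5.1% at 10% loss and 16.2% at 30%. With even timing and linear divergence, it is 4.0% and 9.0%.

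**Effect of the 15-letter exit rule.** Adding the rule to the simulation, with equal variability in both arms and visit-to-visit correlation of 0.4 to 0.8, left the estimate at −4.15 to −4.37 and the rate at 6.1% to 6.7%. The bias was not reversed.

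Unequal exits are different. Suppose each excess Group I exit carries forward a 15-letter loss that would otherwise have recovered. An excess share x then moves the estimate by −15x. Offsetting a shift of 0.64 to 1.0 letters needs x = 0.64/15 to 1.0/15, which is 4.3% to 6.7%, or 1.5 to 2.4 of 36 patients. A larger excess reverses the direction.

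**The case against.** A reader might infer that LOCF here always pulls the estimate towards zero and always inflates false non-inferiority. The documents do not support that.

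- **Exit rule.** Patients who leave under {11b} after a large loss carry a poor value to month 12. If Group I is truly worse, such exits could well be more frequent there, and about two extra would cancel the shift. This stands and limits the claim about direction.
- **Assumed inputs.** Drop-out timing, divergence pattern and the reading of 5 letters as a margin are not in the article. The 9% needs every drop-out to leave by month 3, which nothing suggests. This stands, so the size is a range.
- **Late leavers and a zero effect.** Late drop-outs carry most of the difference, and there is no shift if the true difference is zero. Both are correct, but the type I error of a non-inferiority test is judged at the margin.
- **Estimand.** A patient who leaves before day 90 never received a differing treatment. If outcomes are followed by assignment regardless of treatment, a near-zero contrast for that patient is defensible. This stands in part. But a month-2 acuity soon after loading injections is still not a month-12 outcome, and LOCF reflects nothing that happens to the patient after leaving.
- **SAP content.** A tipping-point analysis is ordinarily left to the SAP, which is not shown. Its absence is no fault here. LOCF, however, is fixed in the article itself.

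**Conclusion.** The point holds in a conditional form and should be fixed. With roughly balanced drop-out, LOCF is likely to be anti-conservative. At the planned 20% loss, a true deficit of 5 letters is estimated at about 4.0 to 4.7 letters, and the false non-inferiority rate is about 4% to 9% instead of 2.5%. This rests on 5 letters being the margin, SD 6.53, 36 per arm, and the assumed drop-out timing and divergence.

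Confidence that LOCF suits this design poorly is higher than confidence in the direction of the bias, which is medium. It would be wrong to conclude that this trial's result must be biased in favour of Group I. The number, timing and balance of actual losses are not reported, and unequal exits after large vision losses could cancel or reverse the shift. What is established is that LOCF makes the conclusion depend on who leaves and when.

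**What to change.** Before unblinding, replace LOCF as the primary method by one of the following:

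- a likelihood-based repeated-measures model on the observed scheduled BCVA values, with treatment by visit and baseline BCVA by visit; or
- multiple imputation by arm.

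Test the month-12 contrast against the stated 5 letters, named explicitly as the margin if that is what is meant. Keep LOCF as a sensitivity analysis. A tipping-point analysis is optional.

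The covariance needs care. An unstructured matrix over 12 post-baseline visits has 12 × 13/2 = 78 parameters, and only about 56 completers are expected. Prespecify a simpler structure or a reduced set of visits.

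A repeated-measures model also uses the low value that triggers a 15-letter exit as an observation at its own visit, instead of treating it as the month-12 result. It does assume that, given the observed history, leavers would have behaved like those who stayed. The plan should state that assumption.

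No new data are needed, because BCVA is already measured at every visit. The costs are modest programming, a somewhat wider interval and a protocol amendment. Under section {25} an amendment entails a revised consent form, ethics approval and renewed participant signatures.
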